### Safety aspects

The published case series using daratumumab in autoimmune diseases have reported good tolerability. The relatively high frequency of **infusion-related reactions (IRR)** seen in multiple myeloma, especially at first infusion, has not been observed as a clinical problem in the small published series of autoimmune conditions, possibly due to the low number of plasma cells in bone marrow and tissue niches compared to multiple myeloma patients who often carry a high tumor burden.

Moreover, aggravation of neutropenia and thrombocytopenia, which has been a concern during multiple myeloma treatment with daratumumab and concomitant chemotherapy, has not been reported in the case series of daratumumab monotherapy in autoimmune diseases.

**Hypogammaglobulinemia** from repeated anti-CD38 antibody intervention and plasma cell depletion may be a matter of concern, especially with long-term treatment. We do not anticipate that this will be a clinical problem when administering a mere four injections, but we will assess immunoglobulins regularly through follow-up, and also measure IgG subclasses at baseline and at the end of follow-up.

We will assess vaccination status with titers of antibodies to tetanus, diphtheria, pertussis and Covid-19, at baseline and repeated at end of follow-up (52 weeks).

Because daratumumab has not been used for ME/CFS, we will assess any occurrence of **anti-daratumumab antibodies (ADA)**, in plasma samples 2 weeks after the fourth injection (at week 20). Plasma samples will be screened for antibodies binding to daratumumab and the titer of any confirmed positive samples will be reported.

The efficacy and safety of the anti-CD38 antibody daratumumab in ME/CFS is unknown. We do not know whether the drug will be beneficial. In addition to high expression of plasmablasts and long-lived plasma cells, CD38 is also expressed on diverse subsets of B- and T-lymphocytes, including B-regulatory cells. Therefore, all biological and clinical effects may not be foreseen.

Although the tolerability in known autoimmune diseases, assessed from the small case series published so far, has been good, we do not know if there will be other side effects in ME/CFS. In theory, some patients could experience worsening of the disease. With this in mind, we will perform a safety review after treatment of the first two patients as described under "Intervention".

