| DSQ-SF                                      |                  | X              | X              | X                | X  | X              | X  | X  | X              | X              | X              |
| Function level                              |                  | X              | X              | X                | X  | X              | X  | X  | X              | X              | X              |
| HADS                                        |                  |                |                | X                |    |                |    |    |                |                |                |
| Download of Fitbit data                     |                  | X              | X              | X                | X  | X              | X  | X  | X              |                |                |
| NIRS assessment n                |                  |                | X              |                  |    |                |    |    |                |                |                |

a Full clinical assessment by investigator incl. laboratory tests, AE assessment and laboratory tests

b Telephone consultation by study nurse or investigator 2 days prior to treatment. Assessment of AEs and fitness for treatment.

c Telephone consultation by study nurse or investigator, monthly after treatment. In the case of AEs of CTCAE grade >1 which require clinical examination and/or extra laboratory workup, visit will be performed in outpatient clinic and not by telephone.

d Assessment by study nurse or investigator on day of treatment, prior to injection. Assessment of AEs and fitness for treatment.

e Classified by CTCAE version 5.0

f See protocol: Laboratory tests at baseline

g Hb, TC, DC, TBC, CRP, Na, K, Ca, Mg, P, Glu, Creatinine, eGFR, ALAT, ALP, GT, bilirubin, albumin.

h Plasma samples for anti-daratumumab antibodies

i Serum immunoglobulins (IgG, IgA, IgM) and lymphocyte subtypes in peripheral blood (CD19, CD3, CD4, CD8, CD56/CD16, ratio CD8/CD4)

j IgG subclasses (IgG1, 2, 3 and 4) and vaccination status: titers of antibodies to tetanus, diphtheria, pertussis and Covid-19.

k 6 ml EDTA plasma, 6 ml EDTA blood, 3x10 ml serum, 2x9 ml Tempus blood RNA

l 6 ml EDTA plasma, 2x10 ml serum

m On clinical indication only

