### **Design**

An exploratory pilot study of six patients with moderate to severe ME/CFS. After inclusion, there will be an initial 12-weeks observational run-in period, followed by administration of 4 subcutaneous injections of the anti-CD38 antibody daratumumab with 2-week intervals. Patients will be subject to clinical follow-up for 40 weeks from start of intervention. Four additional patients will receive the same intervention, and if they show improvement of ME/CFS symptoms by clinical evaluation six weeks after the fourth injection (at study week 24), they will receive three additional maintenance daratumumab injections at weeks 26, 34 and 42.

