### Daratumumab intervention

After 12 weeks’ run-in, patients will start intervention.

The first two patients will receive two subcutaneous injections of daratumumab two weeks apart, followed by an observation period of four to six weeks. If there is no serious, unexpected toxicity, we will proceed with another two injections two weeks apart.

After these two patients have received the planned four daratumumab subcutaneous injections, the Safety board will review the data.

Subject to a favorable Safety board review, the pilot study will proceed with the four remaining patients, who will receive four subcutaneous injections of daratumumab two weeks apart.

Thus, all patients will receive in total four subcutaneous injections of daratumumab.

According to a second amendment to the protocol, among four additional patients included, provided clinical improvement at week 24, these will receive additional three daratumumab injections, at weeks 26, 34 and 42, and with extended follow-up until week 72.

The injections will be administered in the outpatient clinic in the Department of Oncology and Medical Physics at Haukeland University Hospital.

Oral premedication will be given at least one hour before daratumumab injection. Before the first daratumumab injection: Dexamethasone 10 mg orally, Cetirizine 10 mg orally, Paracetamol 1 g orally, Montelukast 10 mg orally. Also, at least 20 minutes before daratumumab: Dexchlorpheniramine 5 mg iv.

On the following two days (2 and 3): Dexamethasone 4 mg orally.

Before the second and subsequent daratumumab injections, if no reaction to the first injection: Dexamethasone 10 mg orally, Cetirizine 10 mg orally, Paracetamol 1 g orally.

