#### Daratumumab dosing and administration

The anti-CD38 antibody daratumumab has not been tested previously in ME/CFS patients.

During recent years, small phase II studies have been published evaluating daratumumab in several autoimmune diseases, among them patients refractory to treatment including rituximab, cyclophosphamide and other immunomodulatory drugs.

In autoimmune hemolytic anemia (44), anti-phospholipid syndrome (45), treatment-refractory autoimmune cytopenias, cold agglutinin disease and other autoimmune diseases (ITP, systemic lupus, anti-CASPR2 encephalitis, rheumatoid arthritis), daratumumab has shown high efficacy in case series (46). In systemic lupus erythematosus, daratumumab was effective and clinical responses sustained by anti-BAFF (belimumab) maintenance treatment (47).

The use of daratumumab in ME/CFS is based on the pathomechanistic model suggesting that ME/CFS is a variant of an autoimmune disease with a role for autoantibodies, produced by long-lived plasma cells.

It is presently unknown what would be the optimal administration and dosing schedule in ME/CFS. Subcutaneous daratumumab 1800 mg is in multiple myeloma equivalent to intravenous daratumumab 16 mg/kg. Subcutaneous daratumumab in monotherapy has a half-life of 20.4 days.

We have based the suggested dosing schedule on the experiences from the above-mentioned studies in established autoimmune diseases. In these small case series of patients with warm-type autoimmune hemolytic anemia (wAIHA), the daratumumab administrations span from one, two, four, six and more than ten administrations, summarized in (46).

In one study of four patients with autoimmune hemolytic anemia (44), patients received repeated daratumumab infusions up to a maximum of six doses, including one patient who stopped treatment after three administrations due to a very good response, with lasting responses to end of follow-up after one year in two patients, and with no major side effects.

In other autoimmune diseases, pilot case reports have used four doses (immune-mediated thrombocytopenia after allogeneic stem cell transplantation; anti-phospholipid syndrome), four daratumumab doses (systemic lupus erythematosus) followed by anti-BAFF antibody belimumab maintenance, 10 administrations (anti-NMDA encephalitis) and 13 administrations (anti-CASPR2 encephalitis), summarized in (46).

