**In addition:**

At the **20-week visit**, plasma samples for determination of anti-daratumumab antibodies will be collected.

At the visits at **12, 16 and 20 weeks, and if given maintenance at weeks 26, 34 and 42:** s-HCG.

At the visits at **weeks 14, 16, 20, 32 and 52, and if given maintenance at weeks 26, 34 and 42:** serum immunoglobulins (IgG, IgA, IgM) and lymphocyte subtypes in peripheral blood (CD19, CD3, CD4, CD8, CD56/16, ratio CD8/CD4).

Also at the **52 week visit:** IgG subclasses (IgG1, 2, 3 and 4), and vaccination status with titers of antibodies to tetanus, diphtheria, pertussis and Covid-19.

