### Biobank samples during follow-up

**At 12, 20, 32 weeks:**

**If receiving additional maintenance injections: at weeks 12, 20, 34, 42:**

1 x 6 ml EDTA-Plasma

2 x 10 ml Serum

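### Anti-daratumumab antibodies are sampled once, at a calendar week that does not fit the first two patients and comes before every maintenance injection

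*Protocol*

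**What the plan says.** The Safety aspects section of the protocol gives the reason for the test (the drug is new in this disease) and its timing: "in plasma samples 2 weeks after the fourth injection (at week 20"). The paragraph headed In addition, under Assessment during follow-up, says that at the 20-week visit "plasma samples for determination of anti-daratumumab antibodies will be collected". In both Schedules of activities, footnote h ("Plasma samples for anti-daratumumab antibodies") is attached to week 20 and to no other week. Samples are to be screened, and the titre of confirmed positives reported. No assay drug tolerance is stated.

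On injections, the Design section says "there will be an initial 12-weeks observational run-in period", so treatment starts at week 12. Under Daratumumab intervention, the first two patients receive two injections two weeks apart, "followed by an observation period of four to six weeks", and then two more injections two weeks apart. The next four patients are those "who will receive four subcutaneous injections of daratumumab two weeks apart". The four added patients follow the same course and, if improved at week 24, receive three further injections at weeks 26, 34 and 42.

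Daratumumab dosing and administration states: "Subcutaneous daratumumab in monotherapy has a half-life of 20.4 days".

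**The concern.** The sample is defined in two ways, by calendar week and by distance from the fourth injection. The two agree only if nothing delays the injections, yet for the first two patients the protocol itself prescribes a delay.

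The antibody test was also not carried into the maintenance phase. The current text adds immunoglobulins, lymphocyte subsets, pregnancy tests and routine laboratory tests at weeks 26, 34 and 42, and biobank plasma at weeks 34 and 42, but no antibody sample. The patients with the most exposure, who are re-exposed after an eight-week interval, are not tested after it.

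The protocol says it will look for any occurrence of these antibodies. It also says the pilot should provide the safety information needed to plan a larger study. If the only result is a negative at week 20, it could be carried forward as broader evidence than it is.

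**Working it through.** **1. The plan's own figure.** Start week 12 (Design) plus three intervals of 2 weeks gives injection 4 at week 12 + 6 = 18. Adding 2 weeks gives week 20, so the stated timing reproduces for the uninterrupted schedule.

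**2. First two patients.** Inputs are from Daratumumab intervention: injections 1 and 2 at weeks 12 and 14, a gap of 4 to 6 weeks, then two injections 2 weeks apart.

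| | 4-week gap | 6-week gap |
|---|---|---|
| Injection 3 | 14 + 4 = week 18 | 14 + 6 = week 20 |
| Injection 4 | week 20 | week 22 |
| Week 20 relative to injection 4 | same day | 2 weeks before |
| Two weeks after injection 4 | week 22 | week 24 |

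No gap in the stated range makes week 20 fall two weeks after injection 4.

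**3. Maintenance.** There are 4 + 3 = 7 injections. Those at weeks 26, 34 and 42 follow the week-20 sample, which is 3/7 = 43%. The last comes 42 − 20 = 22 weeks after it.

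**4. Drug present at sampling.** Equal doses are superposed with first-order decay:

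R(t) = Σ 0.5^((t − tᵢ)/20.4), with t in days and R in dose-equivalents.

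The half-life of 20.4 days is the protocol's. Instantaneous absorption is an assumption, varied below. Over 14 days, 0.5^(14/20.4) = 0.621.

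Standard schedule (weeks 12, 14, 16, 18):
- just after injection 4: 1 + 0.621 + 0.386 + 0.240 = 2.25
- week 20: 0.621 + 0.386 + 0.240 + 0.149 = 1.40, which is 1.40/2.25 = 62% of peak
- week 32 (84 days later): 1.397 × 0.0576 = 0.080, about 17-fold lower than at week 20
- week 52 (224 days after week 20): 0.0007

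With maintenance:
- before the week-34 dose: 0.149 from week 26 + 0.050 carried over = 0.199
- before the week-42 dose: 1.199 × 0.149 = 0.179
- week 52 (70 days later): 1.179 × 0.0927 = 0.109

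The documents give no absorption rate. With assumed absorption half-lives of 1, 2 and 4 days, week 20 on the standard schedule becomes 73%, 81% and 90% of peak. For the first two patients, the level at week 20 before any injection that day is 50–73% of their own peak with a 4-week gap and 21–34% with a 6-week gap, over the same absorption range.

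**The case against.** The strongest reply is that the injection anchor comes first in the Safety aspects sentence and the week only in brackets. Assessment during follow-up also places the 20-week visit after the fourth injection. A sensible site would follow the injection. The stale week label is part of a wider omission: the Safety board/safety review section also still has the first two patients completing all injections at week 18–20. This is fair as to cause. It does not remove the contradiction, because the In addition paragraph and footnote h give week 20 alone.

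Second, antibodies are not an endpoint. The primary outcome is treatment-emergent adverse events, and no stopping or safety-board rule depends on the antibody result. Maintenance applies to at most four patients, who keep their other safety tests. This stands and limits the weight of the point.

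Third, plasma is stored at later visits and might be tested afterwards. It might, but the protocol does not plan it.

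Two stronger readings are tempting and are not supported. A reader might infer that the sample is taken when drug is near its maximum, so that antibodies will probably be missed. With instantaneous absorption, week 20 is 62% of peak. It approaches 90% only under an absorption half-life that the protocol does not give, and it is 21–34% for a first-two patient with a six-week gap. A reader might also infer that a negative result is worthless. That would need the assay's drug tolerance, which is not stated; if the assay tolerates the level present, a negative result is informative for that date.

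**Conclusion.** The point holds on two facts that need no model. For 2 of the 10 patients the stated week and the stated interval cannot both be met. For patients given maintenance, up to 3 of 7 injections follow the only sample, so the plan cannot detect antibodies that arise on re-exposure, whatever the assay.

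The drug-level calculation is supporting context. It shows substantial residual drug at week 20 on the standard schedule and far less at later visits where plasma is already drawn. It rests on the stated half-life, equal doses and an assumed absorption rate. No false-negative rate can be derived from it.

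A negative week-20 result therefore cannot exclude later-onset or post-maintenance antibodies, while a confirmed positive remains informative. This is a gap in a named supporting safety assessment. It should be corrected, but it does not affect the primary outcome.

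**What to change.** In Safety aspects, in the In addition paragraph and in footnote h, define the sample as taken two weeks after the fourth injection, whatever the calendar week. Reconcile the week-20 label, and the week 18–20 in Safety board/safety review, with the first two patients' schedule.

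Add antibody testing on plasma already scheduled under Biobank samples during follow-up: weeks 32 and 52 without maintenance; weeks 34 and 42 (drawn before injection) and week 52 with maintenance. That section already lists the maintenance draws ("If receiving additional maintenance injections: at weeks 12, 20, 34, 42").

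The added testing costs at most 6 × 2 + 4 × 3 = 24 assays, with no added visits. Biobank donation has its own consent form, so check that it covers this use. For the first two patients, the injection-anchored sample falls at weeks 22 to 24, where the schedule has no clinic blood draw. Their 20-week visit would have to move with the injection, or one draw be added. If they have already passed that point, their stored plasma from weeks 32 and 52 is what remains. No dose or treatment rule changes.

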### Benefit/ risk assessment

Patients with moderate (mainly housebound) or severe (mainly bedridden) ME/CFS suffer a very high symptom burden, where even minimal physical or mental activity can trigger a major aggravation and post-exertional malaise. Comparing patients with different chronic diseases, several studies have shown that ME/CFS patients report the highest levels of symptom burden (4, 5). Patients are often cut off from social relations, work or education, and there are major implications including financial difficulties for both patients and caregivers.

The health system has little to offer these patients, and there is a general lack of recognition of the disease, which is largely due to the lack of scientifically approved pathomechanisms, objective biomarkers, and standard effective treatments. Due to the lack of uniformly accepted disease mechanisms, there have been very few clinical intervention studies. Few research groups worldwide have performed interventional studies using immunomodulatory drugs in ME/CFS. This is in sharp contrast to the magnitude of the ME/CFS problem in society, affecting 0.1-0.8% of the population. Thus, there is an urgent need for clinical intervention trials based on scientifically sound hypotheses.

### Possible benefits

The participants will gain access to a new and explorative treatment for ME/CFS, and may experience a beneficial effect on the disease course and symptoms. The patients will undergo a thorough clinical assessment before inclusion and close follow-up for the 12-month study period. After end of study, we will continue to monitor any ongoing clinical response or side effects.

The pilot study will give information of feasibility and possible toxicity, and can also indicate any possible beneficial effects for ME/CFS patients. Such information is necessary to plan a future larger study among ME/CFS patients aiming to verify or refute clinical efficacy.

If daratumumab intervention were to show a beneficial clinical effect on ME/CFS symptoms and disease course, this could be of great importance for a large patient group estimated to 15 to 20 million worldwide. Trial data may also pave the way for elucidation of disease mechanisms, which may form a basis for further therapeutic strategies and for recognition of the ME/CFS disease in medicine as well as in society.

### Possible risks

The participants may experience side effects from the intervention. We cannot be certain that the anti-CD38 antibody treatment will be associated with a beneficial disease course, and patients could in theory also experience worsening of their ME/CFS symptoms.

A lack of clinical response may represent a psychological burden to the patients.

For patients with moderate (mainly house-bound) or severe (mainly bedridden) ME/CFS, participating in a clinical trial may cause temporary worsening due to the stress involved in performing study-specific procedures, such as travelling to the hospital, taking blood samples, receiving subcutaneous interventions and completing questionnaires.

### Efforts to reduce risks

Our research group, based in an oncology department, has access to the necessary treatment and laboratory facilities, and we have clinical experience with follow-up of ME/CFS patients as well as extensive experience with immunomodulatory drugs. We will make efforts to reduce the stress and burden for patients participating in the pilot study, with facilitation for treatment in the outpatient cancer ward. The patients will have direct access to the study management throughout the study period, and will also be able to contact the doctor on duty at the Dept. of Oncology, Haukeland University Hospital if and when necessary.

The participants will undergo regular clinical and laboratory assessments as outlined in the protocol. They will be observed in the outpatient clinic for 6 hours after the first injection, and at least 2 hours after the remaining 3 injections. They will receive pre-medication before daratumumab injections to minimize the possibility for injection-related reactions. Measures will be taken to prevent complications such as virus reactivation and interference with pre-transfusion screening, as outlined under *Intervention* and *Blood typing*.

The first two patients will receive two subcutaneous injections of daratumumab two weeks apart, followed by an observation period of four to six weeks. If there is no serious, unexpected toxicity, we will proceed with another two injections two weeks apart.

After these two patients have received the planned four injections of daratumumab, and before the remaining four patients start intervention, an independent Safety board will perform a formal assessment on safety.

We have since 2016 discussed the concept of plasma cell targeting using the monoclonal anti-CD38 antibody daratumumab ME/CFS, but have delayed an application because there has been limited published data on the use in non-malignant indications. However, the general

impression from recent studies using daratumumab in several autoimmune disease, is that the drug is well tolerated with a favorable toxicity profile, and with good efficacy in antibody-mediated diseases in which the autoantibodies are produced by long-lived plasma cells. There have been few infusion-related reactions, which are relatively often seen in multiple myeloma.

This pilot study is explorative, aiming primarily to assess feasibility and possible toxicity, and to indicate possible beneficial effects. The low number of participants prevents firm conclusions for efficacy, but may provide the rationale for performing a larger clinical trial.

Considering the quality of life for patients with moderate to severe ME/CFS, we believe that assessment of the anti-CD38 treatment principle in a small pilot study for evaluation of safety and possible effect is both justified and important.

